**24.3 \* How, when, where and by whom potential subjects will be approached:**

Caregivers will be approached in the urgent care patient clinic room or waiting room by the study research assistant and a study designated trained ZSFG Health Advocate research assistant and asked whether they are interested in talking about participating in a study on the effectiveness of the ZSFG hospital Health Advocate program. If so, patients will be screened for eligibility. In clinic rooms, while waiting for the provider, the research assistant will consent eligible families and complete study activities with the assistance of the study designated ZSFG Health Advocate research assistant. If the clinic visit ends before study activities are completed, the research assistant and the designated ZSFG Health Advocate research assistant will walk the family down the hall to the research office where the remaining study activities will occur. All study activities will be deferred for provider-patient interactions. This is how we ran our initial study in the Peds Primary and Urgent Care Clinics and this was well-received by clinic staff.

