## 16.0 Procedures

**16.1 \* Procedures/Methods (Help Text updated 9/13) For clinical research list all study procedures, test and treatments required for this study, including when and how often they will be performed. If there are no clinical procedures, describe the Methods:**

All patients in ZSFG Peds Urgent Care during study hours meeting inclusion criteria will be asked by a designated study research assistant accompanied by a study designated trained SFGH Health Advocate Research Assistant (HARA) if they are interested in the study. (See Introduction Script attached.) If there is time in the urgent care private patient room (where there are often long waiting periods for providers), the research assistant will review consents and HIPAA authorization forms with family. Otherwise, following the clinic visit, the study research assistant will escort interested patient families to the ZSFG Health Advocate office on ZSFG 6A (on the same floor and down the hall from the urgent care clinic) for eligibility review and consent process. The study research assistant will assign eligible participants a study ID#, which will be stored in a password protected REDCap file on the study's encrypted and password-protected laptop.

The Research Assistant will review consent with eligible caregivers and patients old enough to participate in consent process. Consent will include documenting study ID, completing caregiver name and contact information and child MR#. (NB: Any duplicate MRN will not be eligible for participation.) One consent form will be used for participants randomized into the intervention arm or the control arm of the study (See attached).

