Consenting caregivers will be given a copy of the study consent forms. They will also be asked to review and sign a HIPAA authorization form to enable access to separate ZSFG HA surveys/follow up and other health care records. In addition to caregiver consent, children 7 and older also will complete assent forms. (See attached study assent forms.) With caregiver permission, children will be offered entertainment activities including bubbles and age appropriate books, games, and videos. Before caregivers complete health surveys with the Research Assistant and HARA, children 2 yo and over and all caregivers will be given a cup of water and asked to swoosh mouths with water and then swallow water. This needs to be completed 20 minutes before saliva and buccal mucosal cell collection. Following water swoosh, all participating caregivers will complete a baseline survey conducted by Research Assistant and HARA on REDCap using a computer tablet. (See attached documents for baseline and follow up surveys.) There is one self-completion portion of the survey, which includes the Patient Health Questionnaire (PHQ-8) and measures for social support and stress, that participants can read and complete themselves or ask for assistance on. After completing the survey, all participating caregivers and children then will have hair cortisol and oral buccal mucosal cell and saliva samples collected. Participants will then be randomized into the intervention arm or the control arm of the study.

Randomization will occur at the participant level using a stratified randomization method in the computer-based program REDCap. This stratified method will be used to ensure a balance of Spanish speaking families and English speaking families within the groups. After completing the study survey and biomarkers collection, the Research Assistant will leave participant dyads with the HARA for randomization. The HARA will randomly assign participants to either the intervention or the control group. The Research Assistant will have no knowledge of or access to participants' group assignments.

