### 24.2 \* How, when, and by whom eligibility will be determined:

A designated research study assistant located in pediatric urgent care will introduce study and determine initial eligibility based on language and patient age. Once family has expressed interest in the study, the research assistant will ensure family members meet all eligibility requirements by asking questions related to inclusion/exclusion criteria.

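### The role that randomizes families and delivers the intervention also joins the approach to families and may assist at consent; only the Research Assistant is kept from assignments

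*Protocol*

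**What the plan says.** Recruitment (Protocol section 24.3; section 16.1 agrees): caregivers are approached "by the study research assistant and a study designated trained ZSFG Health Advocate research assistant". In the clinic room, "the research assistant will consent eligible families and complete study activities with the assistance of the study designated ZSFG Health Advocate research assistant".

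Eligibility (section 24.2): this belongs to the Research Assistant, since "the research assistant will ensure family members meet all eligibility requirements by asking questions related to inclusion/exclusion criteria". The HARA is not named there.

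Baseline (section 16.1): before randomization, "all participating caregivers will complete a baseline survey conducted by Research Assistant and HARA on REDCap using a computer tablet".

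Randomization (section 16.1): after the survey and specimens the Research Assistant leaves, and "The HARA will randomly assign participants to either the intervention or the control group". The method is stratified randomization in REDCap, and its purpose is stated: "This stratified method will be used to ensure a balance of Spanish speaking families and English speaking families within the groups". No block scheme or block size is given.

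After randomization (section 16.1): the HARA carries out the advocacy intervention or gives control families the written handout. The Research Assistant is to have neither knowledge of nor access to assignments. The HARA has no such restriction, and could not have one for the families that he or she randomizes.

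**The concern.** The plan sees the value of keeping a recruiter ignorant of assignments and arranges this for the Research Assistant. It does not extend the separation to the second person at the approach, who knows the assignments that he or she has made.

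Concealment has to protect the step before randomization. If a person who helps recruit can form an expectation about the next assignment, that person may, without meaning to, encourage one family more than another. The arms could then differ at entry in ways that were not measured, and adjustment for covariates may not remove the difference.

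There is room for such influence. Sections 14.1 and 14.3 expect 3000 people to be consented and screened for 1448 enrolled (1448/3000 = 48%), so about half do not enter. Each intervention family also brings the HARA up to three months of telephone follow-up.

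The joint baseline survey adds a smaller worry. It records social needs, and section 14.4 names the number of social needs as a primary outcome, with power based on change from baseline. An expectation about the arm could colour those baseline answers.

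**Working it through.** The plan states no figure for predictability, so there is none to reproduce. The sample-size figures in section 14.4 are not affected.

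**Inputs.** From the protocol: two arms, an equal split (362 per arm, section 14.4), and language as stratum (section 16.1), which is apparent when a family is approached. Assumed, because the protocol does not say: fixed permuted blocks of 4, 6 or 8 within each language stratum, one observer who sees every earlier assignment in the stratum, and a block size that this observer knows or infers.

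**Correct guesses.** In a block of 2m with m places per arm, the best rule is to guess the arm with more places left and to toss a coin when they are equal. Exactly m assignments in each block move back towards balance, and all of these are guessed correctly. The coin-toss positions number 4^m / C(2m, m) − 1 on average, and half of those guesses are right. Expected correct guesses per block are therefore m + [4^m / C(2m, m) − 1] / 2.

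- Blocks of 4 (m = 2): 2 + (16/6 − 1)/2 = 2.83; 2.83/4 = 70.8%.
- Blocks of 6 (m = 3): 3 + (64/20 − 1)/2 = 4.10; 4.10/6 = 68.3%.
- Blocks of 8 (m = 4): 4 + (256/70 − 1)/2 = 5.33; 5.33/8 = 66.6%.
- No restriction: 50%, because earlier assignments carry no information.

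Enumerating every possible block gives the same values.

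**Assignments known with certainty.** Once one arm is used up, the rest of the block is determined. On average this is a share 1/(m + 1) of assignments: 33.3% for blocks of 4, 25% for 6 and 20% for 8. These figures need the block size to be known.

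**Varying block sizes.** With blocks of 4, 6 and 8 in random order and a guess based only on the running imbalance, simulation gives about 68% correct. Varying the sizes therefore does little on its own against one person who sees the whole sequence.

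**Several HARAs.** If two or three HARAs share the assignments at random and each guesses from his or her own running count, simulation gives 49.8% to 50.4% correct. That rule is crude, and a HARA who also learned colleagues' assignments would do better.

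**Does the wording imply restriction?** Stratified simple randomization does not guarantee balance. With 724 dyads, and assuming two equal strata of 362, the share assigned to intervention in a stratum has standard deviation √(0.25/362) = 2.6 percentage points. That is usually close to half, but not ensured. The stated purpose therefore suggests blocking or a similar restriction, without stating it.

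**The case against.** A reader might infer that one navigator performs every randomization, sees all past assignments and can therefore tell what comes next. The protocol does not support this. Section 24.3 speaks of a designated HARA and does not say that there is only one, or that one HARA sees another's assignments. No blocking is stated. The phrase about balance may be loose wording for stratified simple randomization, in which case the past tells nothing. Block details are commonly left to a SAP or randomization plan, so their absence here is not a fault.

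The HARA's influence on entry is also limited:

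- Section 16.1 has all patients who meet the criteria during study hours asked, so the protocol gives no discretion over whom to approach.
- The Research Assistant alone determines eligibility and is the person described as reviewing consent.
- In section 24.3 the HARA's assistance may apply only to completing study activities and not to consent.
- Social needs are collected in the survey, after consent, so at the approach the HARA would have to guess both need and arm.
- Assignment is made in REDCap only after consent, survey and specimens.
- Section 24.3 says the initial study was run this way and that clinic staff received it well.

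All of this stands, and it makes the point conditional. It does not remove the overlap of roles. Randomizing after baseline prevents exclusion once the arm is known, but does not prevent an expectation at the approach. Asking every family still leaves open how warmly each is asked.

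**Conclusion.** The overlap of roles is stated in the protocol: the HARA joins the approach, may assist at consent, helps with the baseline survey, randomizes and delivers the intervention, and only the Research Assistant is kept from assignments. That assignments can actually be anticipated is not established. The figure of 67% to 71% correct guesses holds for fixed blocks of 8 down to 4, with one person seeing the whole language stratum and knowing or inferring the block size. It is lower if several HARAs share the work and 50% if the sequence is unrestricted. It measures predictability and is not an estimate of bias in any outcome, which the documents give no basis to calculate.

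This is a cheap improvement, worth making because the masked recruiter is already in the room. It is not a demonstrated failure of concealment.

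**What to change.** In sections 16.1 and 24.3, state that the Research Assistant alone approaches families, checks eligibility and obtains consent, and that the HARA joins only after consent is recorded in REDCap. Where staffing allows, have the HARA join after the baseline survey, so that the baseline social-needs answers are also taken without the unmasked role. State that any block sizes are not disclosed to the HARA. The separation of roles does most of the work, since undisclosed or varying block sizes alone leave the sequence fairly predictable to someone who sees all of it.

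The cost is more Research Assistant workload at recruitment and a later first meeting between family and HARA. Taking the HARA out of the baseline survey is a larger change in workflow, because section 16.1 has the two conduct it together; it is therefore a preference here, not a requirement. Sample size, outcomes and the intervention do not change.

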**24.4 \* Protected health information (PHI) will be accessed prior to obtaining consent:**

☐ Yes ☒ No

## 25.0 Waiver of Consent/Authorization for Recruitment Purposes

**This section is required when study investigators (and/or affiliated nurses or staff) recruit their own patients directly.**

**25.1 \* Study personnel need to access protected health information (PHI) during the recruitment process and it is not practicable to obtain informed consent until potential subjects have been identified:**

☒ Yes

If **no**, a waiver of consent/authorization is NOT needed.

**25.2 \* A waiver for screening of health records to identify potential subjects poses no more than minimal risk to privacy for participants:**

☒ Yes

If **no**, a waiver of authorization can NOT be granted.

**25.3 \* Screening health records prior to obtaining consent will not adversely affect subjects' rights and welfare:**

☒ Yes

If **no**, a waiver of authorization can NOT be granted.

**25.4 \* Check all the identifiers that will be collected prior to obtaining informed consent:**

- ☒ Names
- ☐ Dates
- ☐ Postal addresses

- ☐ Phone numbers
- ☐ Fax numbers
- ☐ Email addresses
- ☐ Social Security Numbers\*
- ☐ Medical record numbers
- ☐ Health plan numbers
- ☐ Account numbers
- ☐ License or certificate numbers
- ☐ Vehicle ID numbers
- ☐ Device identifiers or serial numbers
- ☐ Web URLs
- ☐ IP address numbers
- ☐ Biometric identifiers
- ☐ Facial photos or other identifiable images
- ☐ Any other unique identifier
- ☐ None

Note: HIPAA rules require that you collect the minimum necessary.

#### 25.5 \* Describe any health information that will be collected prior to obtaining informed consent:

No records will actually be collected by study personnel before informed consents are obtained. Study staff will ask re: parent/caregiver willingness to participate in study activities.

Note: HIPAA requires that you collect the minimum necessary.

#### 25.6 \* Describe your plan to destroy the identifiers at the earliest opportunity consistent with the research or provide a health or research justification for retaining the identifiers, or indicate and explain that retention is required by law:

Identifiers will be destroyed at study end by erasing all electronic linking files.

## 26.0 Informed Consent

#### 26.1 \* Methods (check all that apply):

- ☒ Signed consent will be obtained from subjects and/or parents (if subjects are minors)
- ☐ Verbal consent will be obtained from subjects using an information sheet or script
- ☐ Electronic consent will be obtained from subjects via the web or email
- ☐ Implied consent will be obtained via mail, the web or email
- ☐ Signed consent will be obtained from surrogates
- ☐ Emergency waiver of consent is being requested for subjects unable to provide consent
- ☐ Informed consent will not be obtained

#### 26.2 \* Process for obtaining informed consent:

- a) The consent will take place in ZSFG Children's Health Center Urgent Care Clinic.
- b) Families will be able to ask questions of the fully bilingual/bicultural Eng/Spanish research assistants before signing consents. They will be able to participate in the study or decline and their decision will not affect the quality of care that they receive.
- c) We will have written consents, assent forms for child participants, and HIPAA authorizations in both English and Spanish.

#### 26.3 \* How investigators will make sure subjects understand the information provided to them:

We will have bilingual research assistants available to answer any questions.

## 27.0 Financial Considerations

### 27.1 Subjects payment or compensation method (check all that apply):

Payments will be (check all that apply):

- ☐ Subjects will not be paid
- ☐ Cash
- ☐ Check
- ☐ Debit card
- ☒ Gift card
- ☐ Reimbursement for parking and other expenses
- ☒ Other:

Specify **Other**:

Families will be offered parking stickers to the 23rd Street parking garage at ZSFG or MUNI passes to assist with transportation for the follow-up visit.

### 27.2 Describe the schedule and amounts of payments, including the total subjects can receive for completing the study. If deviating from recommendations in Subject Payment Guidelines, include specific justification below.

Each participating dyad (caregiver + child) will be paid up to \$100 in gift cards for taking part in this study. Each family will receive a \$50 gift card after each of the two visits.

In instances where families do not return for an in-person follow-up visit and complete only the survey by telephone or online, they will receive a \$25 gift card for the follow-up visit. In these cases, the participating dyad will be paid a total of \$75 for taking part in the study.

Caregivers who complete the key informant interview will receive an additional \$25 gift card at completion of the in-person interview.

### 27.3 Costs to Subjects: Will subjects or their insurance be charged for any study procedures?

☐ Yes ☒ No

If **yes**, describe those costs below, and compare subjects' costs to the costs associated with alternative care off-study. Finally, explain why it is appropriate to charge those costs to the subjects.

## 28.0 CTSI Screening Questions

### 28.1 \* This study will be carried out at one of the UCSF Clinical Research Services (CRS) centers or will utilize CRS services. CRS centers are at the following sites:

- SFGH Clinical Research Center
- Moffitt Adult Clinical Research Center
- Moffitt Hospital Pediatrics & NCRC
- Mount Zion Hospital Clinical Research Center
- Tenderloin Center
- CHORI Children's Hospital Pediatrics & Adult Clinical Research Center
- Kaiser Oakland Research Unit
- SF VA Medical Center Clinical Research Unit

**Please note: Effective 3/1/14, the CRS form will no longer be completed and submitted in iRIS. The CRS budget request form can be found at: <https://accelerate.ucsf.edu/files/crs>**

/BudgetRequest2015.docx. Follow the instructions on the form to submit. Even if you click 'Yes' to this question, the form will no longer proceed to the Clinical Research Services (CRS) Application Form section.

☒ Yes ☐ No

**28.2 This project involves community-based research:**

☐ Yes ☒ No

**28.3 This project involves practice-based research:**

☐ Yes ☒ No

## 29.0 End of Study Application

**29.1 End of Study Application Form** To continue working on the Study Application: Click on the section you need to edit in the left-hand menu. Remember to save through the entire Study Application after making changes. If you are done working on the Study Application: Click Save and Continue. If this is a new study, you will automatically enter the Initial Review Submission Packet form, where you can attach consent forms or other study documents. Review the [Initial Review Submission Checklist](#) for a list of required attachments. Answer all questions and attach all required documents to speed up your approval.
